## Abstract

**Background:**

Homelessness is often described as both a driver and a consequence of poor health, social exclusion and economic marginalisation. The present protocol provides a detailed description of the study *Examining the health situation of homeless people in Berlin: a retrospective analysis of data from the health centre for the homeless of the Jenny De la Torre Foundation from 2006 to 2020* (GIG study). The primary objective of the GIG study is to describe and analyse the social and health situation of homeless people in Berlin.

**Methods:**

A retrospective secondary data analysis of an anonymous full census of medical records for the years 2006 until 2020 from a health centre for homeless people will be carried out. The main outcome is the description and analysis of the social and health situation of homeless people in Berlin. Total and cross-sectional sample characteristics will be presented in a descriptive analysis using Chi-Square Test, Mann-Whitney-U-Test or independent t-Test as appropriate to test (sub) group differences. Further, outcomes will be analysed using finite mixture modelling in order to distinguish different types of social and health conditions. Latent variable regressions will be applied in order to identify sociodemographic and disease-related factors associated with decreasing health conditions.

**Discussion:**

Given the high number of homeless individuals in Germany, it is of great importance to examine their social and health situation in order to gain a better understanding of challenges and needs of homeless people and work on new approaches and solutions to effectively address these.

**Trail registration:**

The study was prospectively registered with the German Clinical Trials Register (trial registration number: DRKS00021172). Registered 26 June 2020.

## Background

Homelessness is an extreme reflection of poverty and social exclusion [1] and represents a complex social and public health challenge [2]. Previous research has acknowledged the difficulty in the assessment of the scale of homelessness across Europe, due to inconsistencies in the definitions of homelessness as well as the variety of methodologies applied in data collection [3, 4]. In 2018 about 678,000 homeless people were living in Germany out of which approximately 41,000 spent at least some of their nights without shelter on the streets [5]. In Berlin, 60,000 people are currently estimated to be homeless [6] of which 2000–6000 sleeping rough [7, 8].

Homelessness is often described as both a driver and a consequence of poor health, social exclusion and economic marginalisation [9–11]. Life on the street or in collective accommodation, shelters or hostels represents a major health burden and is often associated with a variety of health problems [12]. For example, research depicts the consistently high rates of acute infectious and parasitic diseases, diseases of the circulatory, respiratory and musculoskeletal system [13] as well as high rates of blood borne infections such as hepatitis C, HIV, tuberculosis, as well as myocardial infarction and pneumonia [14–16]. In addition to acute conditions, a high percentage of the homeless suffer from multimorbidity and chronic diseases [14, 17] such as chronic pain [18] or chronic obstructive pulmonary disease [19]. A study by Queen, Lowrie, Richardson & Williamson [20] found in a homeless cohort with an average age of 42.8 years comparable levels of multimorbidity with those aged > 85 years in the general population. High prevalence of somatic diseases and harsh living conditions might also explain why homeless people generally suffer from higher mortality rates and earlier deaths [11, 21–23]. Homelessness is also associated with a higher risk of psychiatric disorders such as psychosis, major depression, personality disorders, alcohol dependency and drug dependency [24–26]. The high prevalence of somatic and psychiatric diseases can partially be explained by the various stressors associated with the loss of accommodation such as inadequate health maintenance, risk-prone health behaviours [27] and childhood traumata [28]. There have been a number of studies reporting high rates of smoking [29], as well as high rates of alcohol and/or substance misuse [30, 31]. Additionally, homeless people suffer from food insecurity resulting in a generally poorer diet characterised by higher intakes of salt and lower intakes of fruit, vitamin C and fibre [32]. Another major risk factor is the high exposure to violence and higher chance of injury experienced by homeless individuals [33–35]. Furthermore, medical care is usually provided outside the structures of the regular health care system and not always accessible [13, 36]. Rough sleepers are less likely to be registered with a general practitioner [37] and often do not have access to preventive care such as routine check-ups [38, 39]. The consequence of this lack of access to primary care results in a higher number of emergency department visits, hospital (re) admissions and longer inpatient stays [36, 40, 41]. This aspect is also reflected by the high use of emergency departments for dental problems by homeless people [42, 43].

To sum up, past research acknowledges a variety of health needs among homeless individuals. Despite growing recent evidence on the health status of homeless people, data and results do not allow for comparison across countries. Research on homelessness across the EU suffers from a variety of difficulties due to differences in definitions of homelessness and inconsistencies in applied research methodologies [3, 44–47]. Additionally, for Germany, there is a clear lack of empirical investigations on the social and health situation of homeless people. Further, homeless people are difficult to sample which limits most research and results in small and highly selected samples. A recent review found that previous research is highly selective were participants are often older, male and from a subgroup setting as for example from supervised drug consumption facilities [48]. Thus, there is a clear lack of investigation among women and younger individuals. In response to sampling difficulties, other countries such as Denmark, implemented a Homeless Register, where every contact in homeless shelters is documented [21]. There is a need of unbiased research of the homeless population in Germany. In addition, there is little evidence about the course of the social and health situation of homeless people. It is of great importance to gain better understanding of the social and health situation and needs of homeless people. The project  *Examining the health situation of homeless people in Berlin: a retrospective analysis of data from the health centre for the homeless of the Jenny De la Torre Foundation from 2006 to 2020 *(GIG study) aims to explore cross-sectional and longitudinal data from medical records of homeless individuals in Berlin and provide further insights on that subject’s matter. The objective of the present study is to present a study protocol and to describe potential limitations.

### Aim of the present study

The main aim of the present study protocol is the description of the objectives, design, methodology and potential limitations of the GIG study. The objectives of the retrospective analysis can be summarised as the following: 1) comprehensive socio-demographic characterisation of patients and 2) detailed description and analysis of health status and medical history (including utilisation of social and medical services). Both are analysed cross-sectional and longitudinal. Evaluation of longitudinal data will include analysis of individual courses (intra-individually for patients with multiple measure points), as well as analysis of trends where cross sections are considered over time (inter-individual analysis). In line with the study design (retrospective analysis of medical records), research questions will be examined in an explorative manner, based on type and quality of data available from medical records (document analysis). Among others, we aim to address the following research questions:

#### Objective 1

*O1a: Characterise the sample by age, education, gender, migration background, insurance status, detention experience, type of accommodation.*

*O1b: How often is there a change in the homeless status over time? How does the socio-demographic structure change over time?*

#### Objective 2

*O2a: Which are the most frequent health problems homeless people face?*

*O2b: How is the health and social services utilisation among homeless people?*

*O2c: How often/long are patients receiving care in the health centre?*

*O2d: Is there a change in health or social challenges during the last years?*

*O2e: Is there a change in frequency of specific diseases over time?*

*O2f: Are there associations between extreme social conditions and the health status of individuals?*

## Methods

### Study design

To explore the social and health situation of homeless people in Berlin a retrospective analysis of medical records from the health centre for homeless people of the Jenny De la Torre Foundation will be carried out. An overview of the study design can be obtained from Fig. 1.

**Fig. 1 Fig1:**
[figure not shown]
Overview of the study design

### Study setting

Data will be obtained from medical records collected and provided by the health centre for homeless people. The health centre provides donation-based and low-threshold medical care for homeless people. The centre includes a medical practice with medical specialists from various areas, a dental practice and an ophthalmic practice. Further, the centre offers psychological and social counselling as well as legal advice within various fields. In addition, two meals per day, clothing and a hairdresser are at the disposal of patients. The centre also offers the service of taking passport photographs. Every individual visiting the health centre has to first check in with the doctor’s office. At the first visit a medical record is generated for each person. Every time individuals visit the health centre, the reason of the visit and utilisation of any service is documented in the medical record. If required, patients may be treated anonymously.

### Database and data extraction

Based on the general structure and type of data available from medical records, the main purpose of this step was to build a database structure that allows extracting and entering as much relevant data as possible. Therefore, as part of a preliminary screening, *N* = 50 randomly selected medical records were screened for content and data availability. Groups and variables are designed under consideration of previous research [49, 50]. As a result, we identified eight different data sources that can be extracted from medical records (see Table 1): 1) *floating medical record* (a file that contains all information available), 2) *social and medical anamnesis* (social and medical history of the patient; a standardised form that is filled out by the medical personnel at the first visit), 3) *patient information sheet* (a standardised form that contains information on any change of the homelessness, health insurance status, as well as the receipt of financial support), 4) *doctors letters* (including reports and hospital discharge letters), 5) *psychological report* (patients who make use of the psychological counselling in the centre are documented and a report of the counselling is written by the psychologist), 6) *psychiatric record* (a medical record about the psychological well-being of a patient), 7) *documents provided by the health centre* (doctors certificates or sick certificates), and 8) *others* (any other data available from the medical record). Based on the structure of medical records, a database was created using the software Research Electronic Data Capture (REDCap). REDCap is a browser-based, metadata-driven EDC software for designing research databases. It is secured under data protection law by the Charité – Universitätsmedizin Berlin. The database is accessible online which simplifies the entry of data on site while ensuring data safety and protection. No personal identifying data is collected. During data collection, the survey is pseudonymised. For analysis and presentation of results, anonymised data is used. Data extraction started in July 2020 and will end in July 2022.

**Table 1 Tab1:** Overview of different data sources

***data source***		***topic***	***variables***	***categories***	***related objectives/ research questions***
**1**	**Floating medical record**	General information	status of homelessness/ type of accommodation	own flat, hostel, sleeps at friends/ acquaintances, shelter, carrier housing, sleeping rough, other	O1a, O1b, O2d
			status of health insurance	not insured, insured (type of company)	O1a, O1b, O2d
			birthday	year of birth	O1a, O2d
			number of visits	in total	O1a, O1b, O2d
			number of medical consultations	–	O1a, O1b, O2d
			duration of care (date of first and last visit)	in years	O1a, O1b, O2d
			indications of debts	no, yes	O1a, O1b, O2d
		Utilization of health centre services	medical reason	need of primary care, eye specialist, dentist	O2b, O2c
			counselling	(at risk of) homelessness in need of psychologist, social worker, legal advice	O2b, O2c
			Other	food, new clothes, hairdresser, shower, other	O2b, O2c
		Medical history	diagnosis and provided treatment, medication, further recommendations	date of issue, 3-digit ICD-10-GM code*, prescribed medication by ATC code**	O2a, O2b, O2c, O2d, O2e, O2f
**2**	**Social and medical anamnesis**	Socio demographics	age	in years	O1a, O2d, O2f
			sex	female, male, diverse	O1a, O2d, O2f
			school education	number of school years	O1a, O2d, O2f
			occupational education	unskilled, three-year apprenticeship, technical college degree, university degree	O1a, O2d, O2f
			citizenship	list of 202 countries	O1a, O2d, O2f
			family status	married (living together), married (living apart), single, divorced, widowed	O1a, O1b, O2d, O2f
			family contact	no, yes (parents, siblings, children, other)	O1a, O1b, O2d, O2f
			(un)employment	years of unemployment	O1a, O1b, O2d, O2f
			reason for homelessness	job loss, divorce, debt, mental illness, change of location, detention, rental rate, escape from parental home, lease expired, other	O1a, O1b, O2d, O2f
			source of income	social assistance, basic security, unemployment benefit, pension, newspaper sale, collect bottles, begging, other	O1a, O1b, O2d, O2f
			detention experiences	no, yes	O1a, O1b, O2d, O2f
		Medical history	somatic diseases	3-digit ICD-10-GM code*, date of consultation	O2a, O2d, O2e, O2f
			psychiatric diseases	3-digit ICD-10-GM code* (F00-F99), date of consultation	O2a, O2d, O2e, O2f
			dental health	dental problems, consultation of dentist, date of consultation	O2a, O2d, O2e, O2f
			infectious diseases	hepatitis A, B, C, HIV, sexually transmitted diseases	O2a, O2d, O2e, O2f
			medication	prescribed medication by ATC code**, date of prescription	O2a, O2d, O2e, O2f
**3**	**Patient information sheet**	Change of general information	status of homelessness/ type of accommodation	own flat, hostel, sleeps at friends/ acquaintances, shelter, carrier housing, sleeping rough, other	O1b, O2d, O2f
			status of health insurance	not insured, insured (type of company)	O1b, O2d, O2f
			status of financial support	social assistance, basic security, unemployment benefit, pension, other	O1b, O2d, O2f
**4**	**Doctors letters**	Hospital care	hospital discharge letters	institution, date of admission and discharge, date of issue, 3-digit ICD-10-GM code*, prescribed medication by ATC code**	O1a, O2a, O2b
		Ambulatory care	physician’s letter	date of issue, 3-digit ICD-10-GM code*, prescribed medication by ATC code**	O1a, O2a, O2b
**5**	**Psychological report**	Psychological counselling	reason for counselling	date of issue, agreements (appointment: with social worker, for legal advice, with psychologist, job centre, other)	O1a, O2a, O2b
			diagnosis	3-digit ICD-10-GM code* (F00-F99)	O1a, O2a, O2b
**6**	**Psychiatric record**	Psychiatric record	diagnosis	date of issue, 3-digit ICD-10-GM code*	O1a, O2a, O2b
			medication	prescribed medication by ATC code**	O1a, O2a, O2b
**7**	**Documents provided by the health centre**	Certificates	doctors’ certificates	issued for which institution, date of issue, 3-digit ICD-10-GM code*, prescribed medication by ATC code**	O1a, O2a, O2b
		Reports	any report	issued for which institution, date of issue, 3-digit ICD-10-GM code*, prescribed medication by ATC code**	O1a, O2a, O2b
**8**	**Others**	Other information provided in the medical record	x-ray images, electrocardiogram recordings, pictures, letters, notes, other documents	existing yes, no	O1a, O2a, O2b, O2c, O2f

**ICD-10-GM* International Classification of Diseases German Modification, ***ATC code* Anatomical Therapeutic Chemical Classification System

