### Inclusion and exclusion criteria

Every medical record created in the health centre for homeless people from the year 2006 until 2020 will be entered in the database and included in the analysis (N ≈ 3000). There are no other inclusion or exclusion criteria.

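### Extraction began about six months before the 2006–2020 inclusion period ended, with no common end date for visits, so visit totals and duration of care for still-active patients depend on when their record was entered

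*Protocol article*

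**What the plan says.** The section on database and data extraction gives the calendar: "Data extraction started in July 2020 and will end in July 2022". The inclusion section selects by creation of the record: "Every medical record created in the health centre for homeless people from the year 2006 until 2020 will be entered in the database", about 3000 in all, and adds "There are no other inclusion or exclusion criteria".

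The study setting section explains what creation means: "At the first visit a medical record is generated for each person". The same section says that each later visit is documented in that record, so the file of an active patient keeps growing.

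Table 1, under the floating medical record, lists the number of visits as a total, and "duration of care (date of first and last visit"), in years. Neither has an end date. Table 1 links them to O1a, O1b and O2d, but the question they answer most directly is O2c: "How often/long are patients receiving care in the health centre". O2d and O2e ask about change in recent years and in the frequency of specific diseases.

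The abstract describes an "anonymous full census of medical records for the years 2006 until 2020". The section on pretest and quality assurance mentions a code book, training, supervision and random controls. It does not mention returning to records already entered.

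**The concern.** The inclusion rule fixes whose record is in the study. It does not fix which visits in that record count. Because extraction starts while the inclusion period is still running, the same patient can yield different totals and a different last-visit date depending on when a student reached the file.

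The overlap matters on either reading of the study period. If nothing after 31 December 2020 counts, a record entered in July 2020 still cannot contain visits made later that year. If visits count up to entry, records entered in 2021–2022 carry additional follow-up. The artefact falls at the recent end of the series, which O2d addresses, and the Discussion presents the analysis of trends as a major strength. A later analysis plan cannot recover visits that were never extracted.

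A related point affects O2c. Even with a common end date, the longest duration a record can show depends on the year it was opened, so a raw comparison of duration across intake years would show care becoming shorter even if nothing had changed.

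**Working it through.** **Inputs from the article.** Inclusion period 2006 to 2020, taken as 1 January 2006 to 31 December 2020. Extraction July 2020 to July 2022, taken as 1 July 2020 to 31 July 2022. About 3000 records.

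**Assumptions not in the article.** Uniform entry over the extraction period and uniform record creation over 2006–2020.

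**The plan's own figure.** The Discussion gives 14 years of longitudinal data, which is 2020 − 2006. By calendar dates the span is 15.0 years to the end of 2020 and 14.5 years to the start of extraction. Nothing below depends on this difference.

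**Overlap.** Extraction lasts 2.08 years. Of this, 0.50 year lies before the end of 2020 and 2.08 − 0.50 = 1.58 years after it.

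**Share entered before the end of 2020.** 0.50 / 2.08 = 24%, or about 720 of 3000. Counted in whole months, 6 / 24 = 25%, or 750. This is an upper bound on the number affected.

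**Observation window for one record** = (entry date or cut-off, whichever is earlier) − creation date, in years:

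| Created (January) | Entered 1 July 2020 | Entered 31 July 2022, no cut-off | Ratio | Full window to 31 Dec 2020 | Shortfall if entered 1 July 2020 |
|---|---|---|---|---|---|
| 2006 | 14.50 | 16.58 | 1.14 | 15.00 | 3% |
| 2015 | 5.50 | 7.58 | 1.38 | 6.00 | 8% |
| 2018 | 2.50 | 4.58 | 1.83 | 3.00 | 17% |
| 2020 | 0.50 | 2.58 | 5.2 | 1.00 | 50% |

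The absolute difference is the same in every row: 2.08 years with no cut-off, 0.50 year with a December 2020 cut-off. It is large relative to the window only for recently opened records.

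**Effect on 2020 counts under a December cut-off.** Suppose entry order is unrelated to activity and visits are even over the year. Records entered in July–December 2020 miss on average half of that half-year: 24% × 0.5 = 12% of second-half visits, or about 6% of all 2020 visits. The figure would be larger if active files were entered first and smaller if they were entered last.

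**Share of the spread due to entry date.** With no cut-off and the uniform assumptions, the variance of window length is about 19.0 years², of which entry date contributes about 0.36: 0.36 / 19.0 ≈ 2%. Creation date accounts for nearly all the rest.

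**The case against.** The strongest reply is that the problem is smaller than the dates suggest, and that an unseen document may already have settled it. Much of that stands.

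- A reader might infer that observation windows are chiefly set by the order of data entry. They are not. Entry date explains about 2% of the spread even with no cut-off, and windows from about 0 to 15 years are inherent in an open cohort.
- A reader might infer that differences of about two years are planned. They arise only if visits in 2021–2022 are counted. The article neither says so nor rules it out, and the study title and abstract point to a limit at the end of 2020. The code book may set one.
- A reader might infer that some 750 records lose data. That count rests on uniform entry and includes patients last seen years before. The article does not give the number of active patients, so the number actually affected cannot be derived.
- A reader might infer a false drop in every trend. Socio-demographic items come from a form completed at the first visit, so intake trends do not depend on later visits, and proportions need not fall as counts would.
- A reader might infer that mean years from first to last visit is the planned estimator. Table 1 lists the dates as a variable, and no estimator is stated.

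The study is also exploratory, with no confirmatory hypothesis resting on these variables.

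None of this removes the July–December 2020 overlap. An end-of-2020 limit in the code book would remove the two-year differences, but records entered before that date would still be short unless they were re-opened.

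**Conclusion.** The concern holds in a limited form. On the article's own dates and variable definitions, total visits, last-visit date, duration of care, and visit- or diagnosis-based counts for 2020 depend on entry date for patients still attending in or after July 2020. The effect is at most about 6 months per record if visits count to the end of 2020, and up to about 2 years if they count until entry. About 24–25% of records would be entered before the end of 2020 at a uniform rate, and only those whose patients returned after entry are affected. Records of patients last seen before July 2020 are not.

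The consequence is confined to utilisation and recent-trend results (O2c, O2d, O2e), and within these mainly to recently opened records. It is worth correcting because the missing visits cannot be recovered at the analysis stage.

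**What to change.** State one administrative end of observation for all visits, diagnoses and documents, in the protocol and the code book. Two choices work:

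- **30 June 2020**, before extraction began. Entry date then has no influence. The cost is half a year of data, including records opened in July–December 2020, which would contribute no observation time (about 100 if intake were even: 3000 / 15 / 2).
- **31 December 2020**, with a re-check of active records entered before that date. The cost is a limited second look at early-entered files. It is best done during collection, while data are pseudonymised and before the anonymised analysis set is made.

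Count visits and take the last-visit date only up to the chosen day. The visit total must itself be extracted to that day, because a later date filter cannot correct a single total.

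Where utilisation or duration of care is compared across intake years, use person-time up to the cut-off or a fixed window after the first visit. With the end-of-2020 date, the maximum observable duration falls from about 15 years for records opened in early 2006 to under 1 year for those opened in 2020. This changes the analysis only and needs no new data.
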